## Methods/Design

### Study design

A cluster randomised controlled clinical trial will be carried out, analyst blinded, which compares patients with non-specific LBP treated with a multidisciplinary approach, with a control group receiving only usual clinical care.

### Setting

The trial will be conducted in a primary care setting, PHCCs located in Barcelona, Spain and its surroundings. We will contact all the PHCCs by presenting the study to their staffs and we will invite them to participate. The study will be comprised of at least 38 PHCCs.

### Study population

Eligible patients will be consecutively selected by their GP, who will inform them about the study objectives. All patients who agree to participate will be given written informed consent to sign.

Patients will be included if the current episode of LBP occurs suddenly after a period of a minimum of 6 months without LBP and lasts between 15 days and 12 weeks [15] and if they do not fulfill any of the exclusion criteria [3].

Furthermore, patients have to be between 18 and 65 years old, and understand Catalan or Spanish and will be accessible for at least twelve months.

Patients will be excluded if: they are unwilling to participate in the multidisciplinary intervention trial; LBP coexists with cognitive impairment or severe psychiatric disorders such as psychosis, or if they have severe major depression; any other cause of disability which impedes answering the various questionnaires; they are pregnant or breast-feeding; they might have anti-inflammatory intolerance or allergy; treatment for physical problems in the preceding three months has been given; and they have been referred for intensive functional restoration programmes or if they have a confirmed diagnosis of fibromyalgia.

Furthermore, the GP has to ensure that the patient has no red flag signs or symptoms that are frequently associated with specific LBP or potentially severe illnesses [5,16,17].

Red flags for possible specific spinal pathology are: oncologic disease during the previous 5 years; constitutional symptoms, unexplained weight loss, fever, chills, recent urinary tract infection; history of drug or alcohol abuse, or immunocompromised host; vertebral fracture (previous history of major trauma: traffic accidents or falls from heights: patients with risk factors of osteoporosis, long term treatment with glucocorticoids); inflammatory spondylarthropathy (SpA) (pain of typical inflammatory night-pattern pain which forces the patient to get up from bed, gradual onset of pain before the age of 40, severe morning stiffness, limited low back mobility on the sagittal/lateral plane, possible inflammatory involvement of peripheral joints, family history, extra-articular manifestations: uveitis, iritis, psoriasis, colitis, urethritis).

Red flags for surgical referral: saddle anaesthesia, recent onset of bladder dysfunction or anal sphincter impairment, major or progressive motor weakness, sensory level, or widespread neurological signs.

### Randomisation

In this study a cluster design is used because the intervention is delivered to groups. To minimise contamination, the unit of randomisation will be the PHCC. Those PHCCs who agree to participate will be randomly allocated to control or intervention groups by a random sequence generated by a computer programme in blocks of random size and prepared before recruitment of the PHCC by an independent statistician who will be blind to the PHCCs' identities. The blocking factor was randomly selected between an even number (e.g., 4, 6, or 8) and will vary as the recruitment continues. Primary care physicians will be informed about their allocation after giving final consent to participation.

To minimise imbalance across intervention groups, randomisation was conducted stratifying by percentage of immigrants from developing countries registered in each district. We consider two strata, less than and more than 15% immigrants. This variable is taken as a proxy of socioeconomic level.

### Blinding

During the recruitment, the GP will identify new episodes of sub-acute LBP in patients consulting for this reason and those who meet the inclusion criteria will be allocated to the intervention group corresponding to the centre. To avoid bias, consent to participate will be obtained before the allocation.

Because of the nature of the intervention, GPs were not blind to the patients' allocations. Data analysis will be carried out so that the intervention groups allocated to the patients will be unknown to the analyst.

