### Outcomes

Primary outcomes are:

- *Change in disability measured by Roland Morris disability questionnaire (RDQ) *[20,21]. The primary outcome is change in the score on the Roland and Morris disability questionnaire at three months after onset of pain.

Our study will use the Spanish version of the questionnaire, trans-culturally adapted and validated by the Kovacs Foundation, in collaboration with a team of researchers from various hospitals, including the Kovacs Foundation and different PHCCs. Conducted studies demonstrate the *RDQ *questionnaire is a reliable and sensitive measure to evaluate the disability which LBP may generate, namely the limitations in daily tasks which it may entail. Furthermore, the RDQ questionnaire may perform better in the general population [22]. Total scores are obtained through addition of scores for each selected statement, rating from 0 to 24.

- *Intensity of Pain assessed by Pain Questionnaire Spanish version (Mc Gill Pain Questionnaire, (Melzac, 1975) *[23-27], This is a self-administered questionnaire. It is based on the view of pain perception as multidimensional: sensory-discriminative, motivational-affective and cognitive-evaluative. It rapidly identifies the predominant components of pain perceived by the patients. It covers 62 descriptors distributed along 15 classes and 3 dimensions (sensorial, affective and evaluative). It assesses 3 parameters: Total Intensity score, Current Intensity score and Visual Analogical Scale (VAS). Total Intensity score is obtained by adding each class score. Each class score is obtained from ticking one or none of the descriptors in each class. If one is ticked, it scores 1, and if none are ticked, it scores 0. Total Intensity score, which will be located between 0-14, is obtained by adding these three dimensions. Current Intensity score is obtained from a scale such as Likert, rating from 0 to 5. Analogical Visual Scale rates from 0 to 10.

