- *Quality of Life measured by SF-12*. We will use the Spanish version of SF-12 because for large group studies, the differences in measurement reliability between the SF-12 and SF-36 are not as important and the SF-12 is worthwhile for specific populations based on large sample sizes [28]. The 12 items provide a representative sampling of the content of the 8 health concepts and operational definitions of those concepts, including what respondents are able to do, how they feel, and how they evaluate their health status. The dimensions were physical function (2 items), physical role (2), social functioning (1), emotional health (2), mental health (2), vitality (1), bodily pain (1), general health (1). The answer options on the Likert scale evaluate the intensity and frequency of these dimensions. Time reference in the version used is 4 weeks. Scores rate from 0 for worse health status to 100 for best health status, for each of the dimensions. The questionnaire should preferably be self-administered.

Secondary outcomes are:

- *Duration of the current episode of LBP (pre-study and study duration)*. We will consider the current episode finished when the pain and its impact on the person's daily life is reduced, even when the pain cannot be cured completely [29].

- *Work sick leave (yes or no)*

- *Duration in days of work sick leave*

- *Percentage of change in pharmacological treatments*.

- *Wrong beliefs, inadequate behaviour and work factors assessed by Fear Avoidance Beliefs Questionnaire (FAB) *[30]. Among psychosocial factors associated with LBP, avoidance behaviour of physical activity or work due to fear of pain have been demonstrated to have an influence on the disability. The Spanish version of the FAB questionnaire allows us to quantify beliefs and fears regarding the causes and consequences of pain, with validity and accuracy in patients with LBP. This questionnaire, recently validated, contains 16 statements (five related to physical activity and eleven to work activity), which patients score from 0 to 6 depending on their degree of agreement or disagreement. Thus, higher scores indicate a higher degree of avoidance behaviour. Completion takes around ten minutes and it can be self-administered.

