### Data collection and follow-up

All the outcomes will be measured at the individual level. All participants will be invited to attend the PHCC for outcome assessments. They will be assessed on his/her first visit to the PHCC, and at 3 months, 6 months, and 12 months after the onset of LBP. The timing for the second assessment was chosen because it would detect the patients' situation near the point at which they would become chronic. The timing for the last assessment was chosen because adequate follow-up time has been recommended by many authors[6,13]

At each assessment, an expert trained fellow (a psychologist) will make up to three phone calls at different times during the day to make the appointments. During the visit, he/she will fill out the questionnaires by interviewing the participant, will do Lasegue's maneuvre test, will collect information by reviewing medical records, will contact the patient's GP to inquire about their development (compliance of treatment, sick leave, evolution to chronic back pain) and will resolve any questions about the conduct of research.

On January 2009, a pilot study was carried out. Its completion with 14 participants allowed us to: discuss the inclusion and exclusion criteria and the questionnaires used (length, understanding and acceptance): plan the recruitment of patients to achieve a suitable number of participants per group (5 out of 7 invited to participate, attended); redefine the length and distribution of the contents of the intervention and assess adherence to the intervention.

The recruitment period is six months.

Table 4 gives an overview of data collection. Data were entered in a centralised database by the expert trained fellow and the quality of the data will be revised. Figure 1 shows the trial flow chart of the study.

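### Obtaining patient consent before allocation cannot by itself avoid selection bias when centres are randomised and GPs are told their arm, and the article's account of who completes the outcome questionnaires is inconsistent and claims no masking

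*Protocol article*

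**What the plan says.** On recruitment, the Randomisation section states that "the unit of randomisation will be the PHCC" and that "Primary care physicians will be informed about their allocation after giving final consent to participation". Under Study population, "Eligible patients will be consecutively selected by their GP, who will inform them about the study objectives". The Blinding section has the GP identify new episodes, gives each eligible patient the arm of the centre, and then offers this safeguard: "To avoid bias, consent to participate will be obtained before the allocation". The same section concedes that GPs were not blind. One exclusion criterion is that "they are unwilling to participate in the multidisciplinary intervention trial".

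On assessment, Study design and Blinding claim masking for the analyst only. Under Data collection and follow-up, a trained fellow (a psychologist) conducts the visits: "he/she will fill out the questionnaires by interviewing the participant". The same person reviews the medical records and contacts the GP about compliance, sick leave and progression to chronic pain. In the Outcomes section, the McGill entry reads "This is a self-administered questionnaire", and the SF-12 entry reads "The questionnaire should preferably be self-administered". Both instruments are listed among the primary outcomes. No mode is given for the RDQ, which drives the sample size. The Discussion, when justifying the 20% dropout figure, says that the GPs do both recruitment and follow-up.

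**The concern.** In a cluster trial the allocation belongs to the centre and exists before any patient is approached. Obtaining a patient's consent first protects against selection only if the person choosing and informing patients does not know the arm. Here that person probably does, so the stated safeguard does not do what the sentence claims. A GP who knows the arm can, without intending to, differ in whom he or she approaches and in how the study is described.

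The assessment issue is separate. The outcomes are subjective scores. An interviewer who also reads the record and speaks to an unblinded GP about compliance can easily learn the arm, and the article does not say that this is prevented or that the questionnaires come first.

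At stake is a systematic difference between arms that is not a treatment effect. Multilevel modelling gives a proper standard error under clustering; it does not remove such a difference, and neither would a larger sample.

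**Working it through.** **Recruitment, in order of events.**

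1. A centre agrees to take part and is allocated; its physicians are told the arm after their own consent (Randomisation).
2. GPs at that centre select and inform patients (Study population) and identify eligible episodes (Blinding).
3. The patient takes the centre's arm (Blinding).

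The arm is therefore fixed at step 1, before any patient consents. That the GP knows it at step 2 is inferred from Randomisation and Blinding read together. No sentence says so outright, but no other reading fits well. The most favourable reading of the safeguard is that the patient consents before being told the arm. That limits the patient's self-selection, but not the GP's choice of whom to approach.

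**Assessment, side by side.**

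| Item | Outcomes section | Data collection and follow-up |
|---|---|---|
| McGill | self-administered, without qualification | filled out by the fellow at interview |
| SF-12 | self-administration preferred | same |
| FAB | self-administration possible | same |
| RDQ | no mode stated | same |

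The McGill is a direct conflict. The SF-12 departs from a stated preference. The FAB and RDQ entries do not conflict with interview. Data collection and follow-up gives the visits to the fellow, whereas the Discussion gives follow-up to the GPs.

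**Scale, for illustration only.** The inputs from Sample size are a difference of 2.5 RDQ points, SD 5.7, alpha 0.05 (taken as two-sided), power 0.90, ICC 0.1, cluster size 25 and dropout 20%.

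- The plan's own figure: n per arm before clustering = 2 × (5.7 × (1.960 + 1.282) / 2.5)² = 109.24. Design effect = 1 + (25 − 1) × 0.1 = 3.4. Then 109.24 × 3.4 / 0.8 gives 465 per arm, or 468 if 109.24 is first rounded up to 110. The article states 466, so the figure reproduces, and this point does not affect it.
- Analysed per arm: 466 × 0.8 = 372.8. SE = 5.7 × √(2 × 3.4 / 372.8) = 0.77 points.
- With no true effect and a between-arm bias b, the rejection probability is 1 − Φ(1.96 − b/SE) + Φ(−1.96 − b/SE), by normal approximation.

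| Assumed b (RDQ points) | b/SE | Type I error |
|---|---|---|
| 0 | 0 | 5% |
| 0.25 | 0.32 | about 6% |
| 0.5 | 0.65 | about 10% |
| 1.0 | 1.30 | about 25% |

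The values of b are assumptions; nothing in the article supplies them.

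**The case against.** The article does contain mitigation. Selection is to be consecutive, which limits GP choice if it is followed. The models adjust for baseline scores and patient characteristics. Baseline data are reported by group, and analysis is to follow the CONSORT cluster extension. The article admits that GPs were not blind. The random block sizes and the independent statistician address the allocation of centres, which is not in question. All of this stands, but it reduces or exposes selective enrolment and does not remove it: no check on consecutive selection is described, and adjustment covers only what is measured.

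On assessment, silence about the fellow's masking does not show that he or she is told the allocation; this is a condensed article and its flow chart is not shown. Interview is used in both arms, so mode alone does not bias the comparison. Some remote collection is unavoidable, since telephone calls are allowed for patients who cannot attend. These points also stand. What remains is that masking is claimed only for the analyst, that the described duties make unmasking easy, and that the passages on mode and on follow-up disagree.

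Several stronger readings are tempting and are not supported:

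- In the pilot, 5 of 7 invited people attended. A reader might take the other 2 as a rate of refusal in the intervention arm only. The figure appears to concern attendance at sessions, and under intention to treat an enrolled non-attender stays in the analysis.
- A reader might infer that the bias favours the intervention. If those who decline are milder cases, it would run the other way.
- The unwillingness exclusion might seem to operate only where sessions are on offer. It names the trial, it applies to both arms, and the article does not say what control patients are told.
- It might be supposed that the interviewing psychologist also delivers the sessions. The article does not say so.

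**Conclusion.** The point holds in two limited parts.

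**Recruitment.** The safeguard sentence in Blinding overclaims. Consent before allocation cannot by itself avoid selection bias in this design, because the centre's arm is already fixed and the recruiting GP very likely knows it. This rests on reading Randomisation and Blinding together.

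**Assessment.** Masking is claimed for the analyst alone, and the fellow's contact with records and with the unblinded GP is not sequenced after the questionnaires. The interview procedure contradicts the McGill description and departs from the SF-12 preference. The Discussion contradicts Data collection and follow-up on who does follow-up. It would be too strong to say that all the outcomes are described as self-administered; for the RDQ no mode is stated.

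Neither the size nor the direction of either bias can be derived from the article. The type I error figures show only that a bias well below the 2.5-point target would matter. The point should be corrected, but it does not invalidate the design or the sample size.

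**What to change.** **Recruitment.** Replace the safeguard sentence in Blinding with what is to happen:

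- patients consent and complete the baseline questionnaires before being told the centre's arm;
- both arms use the same information sheet and the same question on willingness to attend the sessions;
- GPs are not blind.

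Keep a log of eligible patients not enrolled, with reasons, report it by arm, and state the remaining recruitment bias as a limitation. This reduces and exposes selection by the GP but does not remove it.

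**Assessment.**

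- Do not give the fellow the centre's allocation.
- Complete the RDQ, McGill and SF-12 at the start of each visit, before record review, compliance questions or contact with the GP.
- Have patients complete the McGill and SF-12 themselves, and preferably the RDQ, with interview or telephone as a recorded exception.
- Reconcile the Outcomes entries and the Discussion with Data collection and follow-up.

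**Cost.** Changes to protocol and form wording and a short screening log; no extra staff. Expect a few more missing items and some mixing of modes. Masking of the fellow will be imperfect, because visits take place at the centre and patients may reveal their treatment. Patients' own knowledge of their treatment remains a source of bias that these changes cannot reach.

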### Intervention Design

Patients allocated to the control group will receive usual clinical care, and individual intervention based on the application of the "Clinical Practice Guidelines in the Pathology of the Lumbar Spine in Adults" recommendations, published by the "Institut Català de la Salut" [16]. Topics covered are explained in Table 1.

**Table 1 T1:** Contents of the clinical guidelines applied in this cluster randomised trial

Clinical Practice Guidelines in the Pathology of the Lumbar Spine in Adults
▪ Patient education, give reassuring and positive information about the benign nature of LBP, offer written information including specific advice.
▪ Advise avoiding bed-rest and encourage the person to be physically active and continue with normal activities as far as possible.
▪ Consider offering a structured physical exercise program tailored to personal preferences
▪ Physical exercise should be introduced gently at first (walking, cycling, and swimming) and progressively increased in intensity.
▪ Recommend attendance at the "Back School" to those patients who have not resumed their daily tasks, after six weeks.
▪ Prescribe pharmacological treatment according to the established guidelines

Notes: LBP = Low back pain

Patients allocated to the intervention group will receive the same individual intervention described for the control group, in addition to an educational booklet "The Back Manual [18]" (transculturally adapted Spanish version of the Back Book [19]) and a biopsychosocial multidisciplinary group intervention.

This group intervention will be carried out by a GP, a nurse, a psychologist and a physiotherapist. The programme consists of 2 sessions of 4 hour duration each and 1 session of 2 hour duration. Each group includes up to 12 participants. Patients will be given a leaflet with detailed information of the contents of each session accompanied by examples and exercises, a compact disc of Jacobson's progressive relaxation technique and an audiovisual. The audiovisual reinforces the educational content of the group sessions, such as postural education and motivational and psychological aspects (thoughts on life values and the organization of time). Details of the biopsychosocial multidisciplinary group intervention and the educational digital video disc (DVD) are included in Tables 2 and 3.

**Table 2 T2:** Components of the biopsychosocial multidisciplinary group intervention

GP + Nurse 2 hours	Objective: Resolve doubts, demystify concepts about LBP and promote adherence to the intervention
Theory program	▪ Basics on anatomy and biomechanics of the spine
	▪ Pain mechanisms
	▪ Causes of pain and predisposing factors
	▪ Type of pain, mechanical, inflammatory, and severity
	▪ Healthy life habits

Practical program	▪ Discuss with the participants the doubts, beliefs and myths about back pain and give positive messages

**Physiotherapist 4 hours**	**Objective: Provide tools on exercises/postures to avoid the pain and the chronic course and improve quality of life.**
Theory program	▪ Body posture and its implication in pain
	▪ Ergonomics
	▪ Benefits of relative rest

Practical program	▪ Diaphragmatic breathing exercises as the basis for relaxation, body awareness and postural control.
	▪ Pelvic floor/gyration exercises.
	▪ Propioceptive and posture awareness exercises.
	▪ Strengthening exercises of the psoas and the posterior chain: Paravertebral muscles, gluteus, ischiotibial muscles.
	▪ Strengthening exercises of abdominal muscles, specially the abdominal transversus, gluteus, spinal extensors and scapular muscles.

**Psychologist 4 hours**	**Objective: Provide participants with cognitive-behavioural therapy techniques**
Theory program	▪ Influences of cognitions, emotions and behaviour in pain

Practical program	▪ Relaxation guidelines and methods
	▪ Cognitive restructuring (Modulation of negative thoughts affecting emotions and pain)
	▪ Use of attention (Increasing attention focus)
	▪ Assertiveness (improving social relationships)
	▪ Problem solving (training in step by step techniques for decision making)
	▪ Time organization and reinforcement of reform activities and physical exercise.
	▪ Life values (increasing concordance between values and behaviour)
	▪ Relapse prevention

Notes: GP = general practitioner; LBP = Low back pain

**Table 3 T3:** Contents of the educational Digital Video Disc

Basics on anatomy and biomechanics of the spine
Causes and mechanisms of pain
Recommendations on dealing with pain and coping with it in daily life
Ergonomics applied to daily life (home, work and leisure)
A series of stretching, strengthening, and flexibility exercises and methods to promote physical activity
Cognitive restructuring (Modulation of negative thoughts affecting emotions and pain)
Use of attention (increasing attention focus)
Assertiveness (Improving social relationships)
Problem solving (training in step by step techniques for decision making)
Time organization and reinforcement of reform activities and physical exercise
Life values (Increasing concordance between values and behaviour)
Relapse prevention

To guarantee the standardisation of the group sessions, only one qualified psychologist and one physiotherapist, both of them with extensive expertise in development of training groups, will apply the intervention in all PHCCs.

